### 2.4. Study Procedure

Participant recruitment will target college students aged 21 and older at the university. The recruitment efforts will include email invitations that introduce this study and invite eligible students to participate. The intervention sessions will be conducted in person. The participants will be randomly assigned to either the experimental group (RESPONSIBLEPLAY^©^: MTM-based intervention) or the comparison group (knowledge-based intervention) using SAS PROC SURVEYSELECT. Participant data will first be imported from an Excel file, and each participant will be assigned a unique ID. Simple random sampling (SRS) will then be conducted using PROC SURVEYSELECT, ensuring equal probability of assignment to either group. A fixed seed (12345) will be used to ensure reproducibility. The function will generate a selection indicator (Selected = 1 for the experimental group and Selected = 0 for the comparison group), which will be used to assign the participants accordingly. The final randomized dataset, including group assignments, will then be exported for implementation.

The intervention will be conducted over three weeks, with one session scheduled per week. Each session will span three days, offering multiple time slots to accommodate the participants’ schedules. This approach ensures that all the participants receive the same intervention content while allowing flexibility in attendance. The first session (Week 1) will include an orientation, completion of the pre-intervention survey, and the start of the intervention activities. The final session (Week 3) will consist of intervention activities followed by the post-intervention survey.

To enhance attendance and engagement, the participants will receive email reminders before each session. Additional reminders will be sent to the experimental group between sessions and after the intervention to reinforce the practice of responsible gambling behaviors. At the eight-week follow-up, the participants will attend a final assessment session, which will be scheduled in advance. Email reminders will also be sent to maximize participation.

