### 2.9. Instrumentation

The survey tool for this research consists of a 54-item questionnaire (Supplement S4) specifically designed and refined through a meticulous two-stage review process conducted by a panel of six experts. These specialists, with expertise in MTM theory, instrumentation, and the target population, evaluated the questionnaire’s face and content validity in two rounds. They assessed the clarity, readability, and relevance of the items, leading to wording adjustments and the removal of one item from the behavioral confidence section. Following these revisions, the panel reached a unanimous agreement on the adequacy of the content and face validity for each MTM subscale. The finalized instrument achieved a Flesch Reading Ease score of 57.4 and a Flesch–Kincaid Grade Level of 8.7, confirming its suitability for the intended audience. In prior studies utilizing this MTM-based instrument among college populations, internal consistency estimates (Cronbach’s alpha) for the subscales ranged from 0.76 to 0.89, indicating acceptable to strong reliability [11].

Participants in this study must complete the 54-item survey based on the Multi-theory Model (MTM) at three time points: before the intervention (pre-test), immediately after the intervention (post-test), and during the follow-up period at eight weeks post-intervention. Prior to participation, all individuals will be required to provide informed consent by signing a consent form. This ensures that the participants understand the purpose of this study, their role, and their rights, including confidentiality and voluntary participation.

The initial questions of the survey focus on the frequency and types of gambling activities the participants had engaged in over the past 30 days. These questions are essential for establishing baseline measurements and serve as screening criteria for this study. The participants are asked to report the number of days they gambled during this period and to specify the types of gambling activities they participated in, such as lotteries, sports betting, poker, and online gambling. This information helps to categorize the participants based on their gambling behavior and ensures that the sample includes individuals who are actively engaged in gambling.

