### 2.11. Per-Protocol Analysis

A per-protocol (PP) analysis may be conducted to evaluate the efficacy of the RESPONSIBLEPLAY^©^ MTM-based intervention under optimal conditions [21]. This analysis includes only those participants who fully comply with the intervention protocol and complete the follow-up assessments. By focusing on this subset of participants, the PP analysis aims to provide a more precise estimate of the intervention’s efficacy. Participants will be included in the PP analysis if they meet the following criteria:Absence of Major Protocol Violations: The participants must strictly adhere to the predefined inclusion criteria and avoid any significant deviations from the study protocol [21].Completion of Prescribed Intervention: Only participants who complete their assigned intervention as designed must be considered [21].Availability of Primary Outcome Data: The participants must have complete data for the primary outcome measure to be included in the analysis [21].

The per-protocol (PP) analysis seeks to confirm the efficacy of the interventions by excluding participants who fail to adhere to the protocol or do not complete this study. This approach ensures that the observed effects can be directly attributed to the interventions, focusing only on the participants who fully comply with the study design. In contrast, the intention-to-treat (ITT) analysis includes all randomized participants, regardless of their adherence to the protocol, providing a more conservative estimate of treatment efficacy. Together, these complementary methods offer a comprehensive view of the intervention’s impact under both optimal and real-world conditions [21].

The decision to conduct only a PP analysis is based on the goal of evaluating the intervention’s efficacy under ideal conditions, where adherence to the protocol is maximized. By focusing exclusively on the participants who strictly follow the study protocol, the PP analysis eliminates the confounding effects of non-adherence or protocol deviations. This approach provides a clearer understanding of the potential benefits of the RESPONSIBLEPLAY^©^ MTM-based intervention. It is particularly suitable for assessing health behavior interventions, as the impact of such interventions can be more accurately observed in a population that fully adheres to the prescribed protocol [21].

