### 3.2. Limitations

While this study introduces a robust framework for promoting responsible gambling behaviors, several limitations must be acknowledged regarding its implementation. First, the reliance on a convenience sample from a single southwestern university may limit the generalizability of the findings. The specific gambling behaviors and environmental influences experienced by the participants may not fully represent those of college students in other regions or demographics. To enhance the external validity of this study, future research should aim to replicate this study across diverse populations and settings to better assess its broad applicability. Additionally, the participants who complete all sessions and follow-up assessments may represent a more motivated or problem-aware subgroup, which could introduce interpretive bias. To address this concern, we will compare baseline characteristics between completers and non-completers to assess the presence of any systematic differences and report these findings transparently in future publications.

This study’s three-week intervention period, although consistent with similar behavior change interventions, may not fully capture the long-term sustainability of responsible gambling behaviors. The eight-week follow-up provides some insight into short-term changes; however, extended longitudinal studies are needed to evaluate the persistence of behavior change and the intervention’s capacity to prevent relapse over time.

Participant attrition remains a significant concern in multi-session interventions, particularly within college populations. While we increased the initial sample size by 50% to accommodate the expected dropout, we acknowledge that actual attrition may exceed this estimate. To address this, we have incorporated several retention strategies, including flexible scheduling, frequent reminders (via email), and graduated incentives to encourage session attendance and follow-up completion. We will transparently report attrition rates at each study phase and perform sensitivity analyses comparing baseline characteristics between completers and non-completers. This will help assess whether retention introduces systematic bias—particularly the concern that the participants who complete all the sessions may represent a more motivated or problem-aware subgroup. These insights will be critical in informing the design and scalability of future studies.

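### The post-test is scheduled only at the end of treatment Session 3, with no described route for a randomised participant who misses that session

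*Protocol article*

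**What the plan says.** All places are in the protocol article.

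- **Pre-test (section 2.4).** It belongs to the first treatment session: "The first session (Week 1) will include an orientation, completion of the pre-intervention survey, and the start of the intervention activities".
- **Post-test (section 2.4).** It belongs to the last treatment session: "The final session (Week 3) will consist of intervention activities followed by the post-intervention survey". Sessions are in person, and each is offered in several slots over three days.
- **Follow-up (section 2.4).** It is a visit of its own: "At the eight-week follow-up, the participants will attend a final assessment session, which will be scheduled in advance". It has its own reminders: "Email reminders will also be sent to maximize participation".
- **Survey requirement (section 2.9).** "Participants in this study must complete the 54-item survey based on the Multi-theory Model (MTM) at three time points", the last two being "immediately after the intervention (post-test), and during the follow-up period at eight weeks post-intervention".
- **Inducements (sections 2.7 and 2.4).** The paragraph on the experimental group gives a USD 20 card after each session and at follow-up. The paragraph on the comparison group gives one USD 20 card at the end of follow-up. Both arms get reminders before sessions; further reminders between sessions go to the experimental group.
- **Retention (section 3.2).** The measures are "flexible scheduling, frequent reminders (via email), and graduated incentives to encourage session attendance and follow-up completion". Attrition will be reported by phase, and completers and non-completers will be compared at baseline.
- **Analysis (sections 2.11 and 2.13).** Section 2.11 contrasts per-protocol with a complementary approach, in which "the intention-to-treat (ITT) analysis includes all randomized participants, regardless of their adherence to the protocol", and then states a decision to do per-protocol only. Section 2.13 plans a two-way mixed ANOVA over the three time points.

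**The concern.** When an outcome survey is the closing item of a treatment session, missing treatment and missing the outcome become one event. The post-test comparison is then a comparison of people who came to Week 3. Section 3.2 itself allows that completers may be more motivated or more aware of their problem than others.

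This matters more if the two arms lose people at different rates or for different reasons. The stated inducements to attend are unequal between arms, and with this placement they act directly on whether the post-test is obtained.

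The planned safeguards do not reach the problem. Slots, reminders and incentives encourage attendance but do not collect a post-test from someone who did not come. Comparing baseline characteristics of completers and non-completers cannot show whether loss depended on how participants responded to the programme. The 50% increase in sample size protects precision, not against bias.

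**Working it through.** **1. What the schedule yields for each attendance pattern.** This follows sections 2.4, 2.11 and 2.13 as written. The ANOVA column assumes the classical form, which needs all three measurements. A likelihood-based mixed model would keep incomplete cases, but none is named.

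| Attendance | Pre | Post | 8 weeks | Classical ANOVA | Per-protocol set |
|---|---|---|---|---|---|
| Sessions 1, 2, 3 and follow-up | yes | yes | yes | kept | kept |
| Sessions 1, 3 and follow-up | yes | yes | yes | kept | out, on a strict reading |
| Sessions 1, 2 and follow-up | yes | **no** | yes | dropped | out |
| Session 1 and follow-up | yes | **no** | yes | dropped | out |
| Sessions 1, 2, 3, no follow-up | yes | yes | no | dropped | out |

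Rows three and four are the point. These people can be measured at eight weeks and the schedule provides for it, but the post-test is not obtained. The classical ANOVA then discards their follow-up too.

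**2. Inducement to attend, by arm (section 2.7 as stated).** Experimental: 3 sessions × USD 20 + USD 20 at follow-up = USD 80. Comparison: USD 20 at the end of follow-up. For attending Session 3 itself, the stated payment is USD 20 versus nothing.

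**3. The plan's attrition allowance (section 2.3).** 20 per group × 1.5 = 30 per group, 60 in total. The tolerated loss is (30 − 20)/30 = 33.3%, or 20 of 60. This covers all attrition and missing data together; it is not an estimate of Week 3 absence. Whether 20 per group is the right requirement is a separate question.

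**4. How large a bias could be (illustration; every input is assumed).** Suppose there is no true effect. Let the outcome, scored so that higher is better, and a latent tendency to attend both be standard normal with correlation r. In an arm that loses the fraction p least inclined to attend, the mean outcome among attenders is r × φ(z_p)/(1 − p), with z_p = Φ⁻¹(p).

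- p = 0.10: 0.1755/0.90 = 0.195
- p = 0.30: 0.3477/0.70 = 0.497
- p = 0.50: 0.3989/0.50 = 0.798

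Spurious difference, experimental minus comparison, in SD:

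| Loss (experimental vs comparison) | r = 0.2 | r = 0.3 | r = 0.5 |
|---|---|---|---|
| 20% vs 20% | 0 | 0 | 0 |
| 10% vs 30% | −0.06 | −0.09 | −0.15 |
| 10% vs 50% | −0.12 | −0.18 | −0.30 |

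For example, 0.3 × (0.195 − 0.497) = −0.09. The sign here goes against the experimental arm because attenders are assumed to do better and the comparison arm to lose more. Reversing either assumption reverses the sign.

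**The case against.** The strongest reply has four parts.

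**The follow-up is not tied to treatment.** A reader might infer that someone who stops attending has no scheduled outcome assessment at all. The documents do not support that. The eight-week assessment is a separate session, arranged in advance for all participants without any condition on earlier attendance, with its own reminders and with payment in both arms. Missing it is ordinary loss to follow-up. For the same reason, the retention measures do not all aim at treatment attendance, since section 3.2 also names follow-up completion. An all-randomised analysis is not ruled out either: pre-test and eight-week data can still come from people who left the sessions. These objections stand, and they confine the point to the post-test.

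**A condensed article may omit make-up arrangements.** This stands in part: an alternative route is not excluded, so the finding can only be that none is described. But the article does state where the post-test is taken, requires all three surveys and lists its remedies for attrition. None of those remedies collects a post-test from an absentee.

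**The per-protocol-only decision would discard the recovered data.** Correct. Changing the schedule alone would not alter the efficacy result planned in section 2.11. But changing the analysis set later cannot supply post-tests that were never taken, so both changes are needed.

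**The harm is conjectural.** Also largely correct. Unequal payments and reminders give a reason to expect unequal attendance but no rate, and the extra reminders are meant to reinforce practice rather than attendance. With equal loss and equal selection the bias is zero.

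**Conclusion.** The point holds for the post-test. As written, a participant absent from Session 3 has no post-test, and capture of that outcome depends on attending treatment under inducements stated for one arm only. The eight-week outcome is affected only indirectly, if a classical three-time-point ANOVA drops people who lack the post-test.

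The size of any bias cannot be derived from the documents. The 0.06 to 0.30 SD range comes from assumed loss rates and correlations and shows only what unequal loss could do. It would be wrong to read the allowance of 20 of 60 as the number expected to lack a post-test, because that figure covers all attrition and missing data.

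The change should be made because it is cheap and because post-tests not taken at the time cannot be recovered. Section 2.5 describes the study as already underway.

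**What to change.** **Section 2.4.** Keep in-session completion for those who attend, so that their survey mode does not change mid-study. For every randomised participant in either arm who misses Session 3, send the same coded questionnaire by email link in a fixed window, for example within 3 days after the last Week 3 slot. Do likewise, in a fixed window, for anyone who misses the eight-week session. State that stopping sessions does not end outcome collection. Record the survey mode.

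**Sections 2.11 and 2.13.** Replace the per-protocol-only decision with an analysis of all randomised participants that uses these data, in a form that keeps people with a missing time point. Per-protocol can remain as a supplement.

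**Cost.** An online version of the existing questionnaire and a minor IRB amendment are needed, with no extra staff or visits. Some surveys will be completed unsupervised, and some absentees will not answer the link, so missing post-tests will be reduced rather than removed.

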### 2.5. Ethical and Data Security

This study adheres to established ethical guidelines and has received approval from the Institutional Review Board (IRB). This protocol is currently underway and has been approved by a southwestern university under IRB Protocol # UNLV-2024-507, dated 14 April 2025. Informed consent will be obtained from all the participants before their involvement, and comprehensive measures will be implemented to ensure the confidentiality of participant information and the security of collected data.

To protect participant anonymity and confidentiality, this study will implement several key measures. Each participant will be assigned a unique identifier code, replacing names on all study materials to ensure data privacy across all phases. All digital data will be securely stored in password-protected files on Google Drive, with access restricted to authorized research team members. Informed consent will outline confidentiality safeguards, and no personally identifiable information will be collected. Any potentially identifiable data will be de-identified before analysis. Researchers will sign confidentiality agreements, and physical data, such as printed surveys, will be stored in locked cabinets. These measures are designed to uphold ethical standards and maintain participant trust.

### 2.6. Strategies to Prevent Cross-Group Influence

To minimize cross-group influence, this study will implement several strategies. Intervention sessions for the experimental and comparison groups will be scheduled separately, and group-specific materials will be clearly labeled and distributed exclusively to each group. The participants will be briefed on confidentiality and instructed not to discuss session content with members of the other group. The research team will actively monitor sessions to ensure adherence to these protocols and address any issues promptly. These measures aim to preserve this study’s integrity and validity.

### 2.7. Interventions

The experimental group will participate in a three-week intervention based on the MTM of health behavior change [10]. This intervention includes role-playing, psychodrama, journaling, and exploring recreational alternatives to address gambling behaviors. Participants will document their gambling-related activities, physical and emotional challenges, and achievements throughout the program. Each session will last approximately 60 min and be held once per week for three weeks. To encourage participation, the participants will receive a USD 20 gift card after each session and again at the eight-week follow-up.

Session 1: This session explores the pros and cons of gambling, emphasizing how the benefits of responsible gambling outweigh its risks. The participants work on building behavioral confidence, developing plans for responsible gambling, and identifying environmental changes that support responsible gambling practices (Supplement S1).

Session 2: In this session, the participants reflect on their emotions related to gambling and explore techniques for transforming negative emotions into positive ones. They receive guidance on journaling and record-keeping as tools for self-awareness and accountability. Additionally, the participants engage in recreational activities as alternatives to gambling and identify sources of social support that encourage responsible gambling behaviors (Supplement S1).

Session 3: The final session features a guest speaker from the Nevada Council on Problem Gambling, who will provide insights and motivation. The activities focus on initiating responsible gambling behaviors over the next eight weeks and strategies for sustaining them. The participants also receive practical demonstrations of techniques to implement and maintain responsible gambling behaviors long term (Supplement S1).

The comparison group will participate in three knowledge-based sessions, each featuring lectures and presentations focused on gambling behavior (Supplement S2). Each session will last approximately 60 min. At the conclusion of the eight-week follow-up, the participants will receive an incentive (a USD 20 gift card) as a token of appreciation and to support their continued learning. The Table 2 describes the alignment of intervention components with MTM constructs and behavioral outcomes.

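### USD 60 of the incentive is tied to session attendance in the experimental arm and none in the comparison arm, while session completion decides who is analysed

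*Protocol article*

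**What the plan says.** Section 2.7 sets the incentive separately for each arm. The paragraph on the experimental arm states: "To encourage participation, the participants will receive a USD 20 gift card after each session and again at the eight-week follow-up". The paragraph on the comparison arm describes the same session load ("The comparison group will participate in three knowledge-based sessions, each featuring lectures and presentations focused on gambling behavior", also about 60 minutes each) and then gives its own payment rule: "At the conclusion of the eight-week follow-up, the participants will receive an incentive (a USD 20 gift card". No payment per session is stated for that arm.

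Section 3.2 gives the purpose of the payments. It lists among the retention strategies "graduated incentives to encourage session attendance and follow-up completion".

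Section 2.4 places the post-intervention survey at the end of the third session. It also says: "Additional reminders will be sent to the experimental group between sessions and after the intervention".

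Section 2.11 defines the analysis set: "This analysis includes only those participants who fully comply with the intervention protocol and complete the follow-up assessments", and "Only participants who complete their assigned intervention as designed must be considered". The section opens by presenting the per-protocol analysis as optional but closes by justifying it as the only analysis. It describes intention-to-treat in general terms without committing to it.

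**The concern.** Randomisation protects the comparison only if the people analysed are still those it produced. Here, completing the sessions is a condition for being analysed, and one arm is paid to complete them while the other is not. By the protocol's own account the incentives are there to raise attendance, so the design gives a reason to expect attendance to differ by arm. Missing session 3 also means missing the post-test, so outcome data can be lost as well.

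Two things are at stake. First, the completers in the two arms may be different kinds of participant, and a comparison between them then carries a selection bias that baseline tests cannot rule out. Second, payment is not among the MTM components in Table 2. The contrast becomes the MTM programme plus paid attendance against knowledge sessions with unpaid attendance, which is not the contrast the trial sets out to test. The extra reminders are a different matter, because Table 2 counts reminders as part of practice for change.

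**Working it through.** **Payments (Section 2.7)**

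| | Experimental | Comparison |
|---|---|---|
| Sessions 1 to 3 | 3 × 20 = USD 60 | USD 0 |
| Eight-week follow-up | USD 20 | USD 20 |
| Maximum total | USD 80 | USD 20 |

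The whole gap lies in the sessions. Because the post-test closes session 3 and cards come after each session, only 2 × 20 = USD 40 has certainly been paid before the post-test is completed. The third card may depend on staying for it.

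**What the plan allows for**

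Section 2.3 raises 20 per group by 50%: 20 × 1.5 = 30. This tolerates a loss of 1 − 20/30 = one third, treated as equal in both arms. No completion rate by arm is given anywhere, so every rate below is an assumption.

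**Illustration 1: selection on motivation, no true effect**

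Suppose a participant completes when a latent motivation exceeds a threshold, and motivation correlates r with a favourable outcome. With completion rate p, the mean outcome among completers is r × h(p), where h(p) = φ(z)/p and z is the normal quantile cutting off the top p. The bias is r × [h(p_E) − h(p_C)], in SD units.

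- For 80% versus 60%: h(0.80) = 0.350 and h(0.60) = 0.644, a difference of −0.294. With r = 0.2 the bias is −0.06 SD; with r = 0.5 it is −0.15 SD.
- Numbers analysed are 24 and 18, so SE = √(1/24 + 1/18) = 0.312.
- Type I error is Φ(−1.96 + |b|/SE) + Φ(−1.96 − |b|/SE), which gives 5.4% at r = 0.2 and 7.6% at r = 0.5.
- For 90% versus 50% (27 and 15 analysed): absolute bias 0.12 to 0.30 SD, type I error 6.6% to 15.5%.
- For equal completion: bias 0 and type I error 5.0%.

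In this model the unpaid arm keeps the more motivated subset, so the bias runs against the experimental arm.

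**Illustration 2: selection on severity, analysed as pre-post change**

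This is closer to the planned mixed ANOVA. Inputs are 30 per arm, no true effect, the correlation of 0.5 from Section 2.3, logistic completion depending on severity, 8,000 replicates and a t-test on change.

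- At 80% versus 60%, the bias is about 0.05 SD and rejection about 5% to 5.5%. The sign depends on whether completion follows baseline or later severity, and on whether one arm or both are selected.
- At 85% versus 55%, with severe cases dropping out of one arm and mild cases out of the other, the bias is about 0.14 to 0.15 SD and rejection about 7%. The sign again reverses with the selection mechanism.
- Rejection as high as about 14% appears in that last scenario only if post-test scores are analysed alone with selection on outcome severity.

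**Wording**

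Section 3.2 calls the incentives graduated. Section 2.7 shows a flat USD 20 per card in both arms, differing only in how many cards are given.

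**The case against.** The strongest case on the other side is that no bias has been shown. The documents give no completion rates by arm, attendance could turn out similar, and under moderate assumptions the type I error stays near 5%. This stands as a limit on size. It does not remove the concern, because the protocol itself relies on incentives to change attendance.

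The payment at follow-up is equal. That is correct: any effect on follow-up attrition is indirect, through who is still attending after three weeks.

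Much of the harm comes from the per-protocol restriction. This is also true in part. Analysing everyone randomised would stop session completion from deciding who is analysed. It would not recover post-tests lost through missed third sessions, nor remove payment as a difference between arms.

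Section 3.2 promises attrition reporting at each phase and a baseline comparison of completers with non-completers, and Section 2.8 applies reach and fidelity tools in both arms. These are useful, but the completer comparison is not said to be made by arm and cannot show differences in unmeasured motivation. ANCOVA on baseline variables has the same limit.

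It could be said that "the participants will receive a USD 20 gift card after each session and again at the eight-week follow-up" refers to everyone. The sentence sits in the experimental-arm paragraph, and the comparison paragraph has its own different rule. If everyone was meant, the two sentences conflict and the text still needs correcting.

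Finally, a reader might infer that payment directly changes how participants answer the surveys. The documents do not support that: the cards are given for attendance, not for particular responses.

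**Conclusion.** The unequal schedule is real, and it acts on the condition for entering the only analysis the article commits to. It is likely to make attendance, post-test completion and the analysis set differ by arm, and it adds a non-MTM difference to the contrast. The firm figures are USD 60 against USD 0 for sessions, and USD 20 against USD 20 at follow-up.

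The size and direction of the resulting bias are unknown. With assumed completion of 80% versus 60%, it is roughly 0.05 to 0.15 SD in either direction with type I error of about 5% to 8%. Larger values need extreme assumptions about completion or about opposite selection in the two arms.

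A reader might go further and conclude that the arms are certain to differ, that the design favours RESPONSIBLEPLAY, or that the false-positive rate is well above nominal. The documents support none of these. The plausible mechanisms point both ways, which makes a positive or a null result harder to interpret but does not predict either.

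**What to change.** Use one identical incentive schedule in both arms, tied to the same four visits (three sessions and follow-up). The preferred form is USD 20 at each visit for everyone. The maximum cost rises from 30 × 80 + 30 × 20 = USD 3,000 to 60 × 4 × 20 = USD 4,800, which is USD 1,800 more, plus an IRB amendment.

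Splitting the present USD 3,000 equally gives 3,000/(60 × 4) = USD 12.50 per visit at no extra payment cost. It lowers the experimental maximum from USD 80 to USD 50, so it is open only for participants who have not yet consented to the current amounts.

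Section 2.5 describes the protocol as underway. If enrolment has begun, equalise from now on, and report session attendance, post-test completion and follow-up completion by arm, separately for participants before and after the change. Make the planned comparison of completers with non-completers within each arm. Reword Section 3.2 so that its description of the incentives matches Section 2.7.
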